## Methods/design

### Design

This study is an unblinded, non-randomized, multi-centre (4 sites), double-arm, controlled trial with 1:1 assignment. The duration of the study is 3 years and includes literature review, development of the app, clinic and patient recruitment, intervention delivery, as well as, data collection and analysis.

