### Exclusion criteria

emergency hip or knee replacement surgery, such as after a fallrevisions or exchange surgeryPatients already received a replacement of another joint in the pastcognitive impairments of all types (as assessed by the attending physician)mental illnesses of all types (as assessed by the attending physician)Patients, who have not downloaded the app when they were admitted to the hospital (intervention group)post-surgical complications, such as infections, allergies, instability, delirium, or otherlimited language skills preventing proper app use or completion of questionnaires

Participants assigned to the intervention group who failed to download or access the app will be excluded. However, project coordinators of the participating hospitals will interview those participants and record their reasons for not engaging with RECOVER-E. These data will be analysed and reported as part of the sample description.

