### Sample size

Based on the primary outcome ADL subscale of the KOOS/HOOS and the assumable clinical relevant change of 10 points [37, 44, 45], we expect that the group using the mobile app in addition to the standard care will improve at least 10 points more than the control group after having undergone TKR/THR 3 months post-surgery.

To allow for separate analysis of patients with knee and hip OA, 58 knee patients and 58 hip patients are required to detect a difference of 10 points on the HOOS/KOOS ADL subscale (SD 15, power = 0.80 and α = 0.05) [37, 44, 46]. Allowing for 20% dropout [47–49], 5% complications post-surgery [50] and 4% erroneous records, a total of 160 patients will be recruited.

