Design and structure of the app were specifically developed to meet the needs of an older target group. However, a lack of patient technology literacy cannot be entirely eliminated, thereby, as a further limitation, negatively affect patient adaptation and compliance to mobile intervention.

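### The recruitment target of 160 makes no allowance for the app-arm patients whom the plan itself excludes for not downloading the app

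*Protocol article*

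**What the plan says.** The Sample size section of the protocol article states that "58 knee patients and 58 hip patients are required to detect a difference of 10 points on the HOOS/KOOS ADL subscale", with the inputs "SD 15, power = 0.80 and α = 0.05". It does not say whether the test is one-sided or two-sided. It then moves from the required number to the recruitment target: "Allowing for 20% dropout [47–49], 5% complications post-surgery [50] and 4% erroneous records, a total of 160 patients will be recruited". The Design section describes a "double-arm, controlled trial with 1:1 assignment".

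The Exclusion criteria contain two items that can only take effect after a patient has been enrolled. One is post-surgical complications. The other applies to the intervention group alone: "Patients, who have not downloaded the app when they were admitted to the hospital (intervention group". The paragraph below the list repeats it: "Participants assigned to the intervention group who failed to download or access the app will be excluded". Coordinators are to interview these patients about their reasons. The Discussion names the exclusion as a limitation and defends it.

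The Data analysis section says that all patients will be analysed by intention to treat. No section gives an expected non-download rate, says that these patients are replaced, or says that they count towards the 20% dropout.

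**The concern.** The recruitment target is evidently meant to absorb exclusions made after enrolment, because complications have a 5% line of their own. The second exclusion of the same kind has no line. The article sets out its whole inflation and the result, so this is not a detail left to a fuller document.

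At stake is whether 58 evaluable patients per joint, and the power of 0.80 attached to them, describe the set of patients that the plan's own rules would leave. The point is about the evaluable number only. The bias from excluding non-downloaders in one arm is a separate matter, which the article acknowledges.

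**Working it through.** **Inputs from the protocol article.** Difference 10 points, SD 15, power 0.80, α 0.05, 58 patients per joint, 160 recruited, losses of 20%, 5% and 4% (Sample size); 1:1 assignment (Design).

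**Derived.** 80 recruited per arm. The 58 per joint become 29 per arm and joint, hence 58 per arm (29 knee + 29 hip). The per-arm 58 is not stated in the article; it follows from 1:1 assignment and happens to be the same number as the per-joint requirement.

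**Assumed.** The app-arm non-download rate q, shown at 5%, 10% and 20%; an even split between knee and hip; non-download independent of the other losses.

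**Step 1: reproduce 58 per joint.** Two-sample t-test, difference 10, SD 15:
- One-sided 5%: 29 per arm, 58 per joint, power 0.806. This matches. The normal approximation gives 28 per arm, 56 per joint.
- Two-sided 5%: 37 per arm, 74 per joint (normal approximation 36 and 72). This does not match. With 29 per arm, two-sided power is 0.704.

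**Step 2: reproduce 160.** Retention = 0.80 × 0.95 × 0.96 = 0.7296. Then 116 / 0.7296 = 158.99, so 159, rounded up to 160. If the allowances are added instead, 116 / (1 − 0.29) = 163.4, so 164, slightly above the stated target. The multiplicative scheme fits better and is used below.

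**Step 3: slack at 160.** Total: 160 × 0.7296 = 116.7 against 116. Per arm: 80 × 0.7296 = 58.4 against the derived 58.

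**Step 4: break-even non-download rate.**
- Total: 116.736 − 58.368 q = 116, so q = 0.736 / 58.368 = 1.3%.
- App arm: 58.368 (1 − q) = 58, so q = 0.6%.

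**Step 5: expected numbers and power at 160 recruited.** App arm = 58.368 (1 − q); control arm = 58.368; half of each per joint. Power is from the noncentral t distribution.

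| Assumed q | App arm | App arm per joint | Total | Per-joint power, one-sided | Per-joint power, two-sided |
|---|---|---|---|---|---|
| 0% | 58.4 | 29.2 | 116.7 | 0.81 | 0.71 |
| 5% | 55.4 | 27.7 | 113.8 | 0.80 | 0.69 |
| 10% | 52.5 | 26.3 | 110.9 | 0.79 | 0.68 |
| 20% | 46.7 | 23.3 | 105.1 | 0.77 | 0.65 |

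Controls stay at 29.2 per joint throughout.

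**The case against.** The strongest reply is that the size of the loss is unknown and probably small. The documents give no non-download rate, and the plan takes steps that should keep it low: owning a smartphone is an inclusion criterion, and coordinators and a hotline help with the download. The margin is also thin for reasons unrelated to this rule. The spare patient comes from rounding 159 up to 160. The expected 58.4 per arm has a binomial SD of √(80 × 0.7296 × 0.2704) ≈ 4, so an arm of 80 has about a 41% chance of ending below 58 with no non-downloaders at all. If the three allowances are added, 160 × 0.71 = 113.6 is short from the start. All of this stands, and it is why the break-even rates show only that nothing was set aside, not that a single exclusion is decisive.

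The undefined 20% dropout might also cover some of these patients, and non-downloaders may be the same people who would miss the three-month online survey. Overlap would make the extra loss smaller than the table shows. But the article does not say that dropout includes them. The 20% is applied to both arms, whereas non-download can occur in one only, and the comparable exclusion was given its own line.

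Three stronger readings are tempting and should not be drawn:
- *That the app arm will fall short of 58.* This needs a rate that the documents do not give, and a per-arm requirement that they do not state.
- *That the promised 1:1 ratio fails.* The article promises 1:1 for assignment, not for the analysed set.
- *That the Discussion predicts poor uptake.* It says that "a lack of patient technology literacy cannot be entirely eliminated" and that this may affect adaptation and compliance. That is not a forecast of how many will fail to download.

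Finally, if the intention-to-treat statement prevails over the exclusion, the shortfall disappears. That is correct, but the two statements cannot both stand as written, so one section has to change either way.

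**Conclusion.** The omission holds: the plan's evaluable size of 58 per joint leaves out a loss that its own exclusion rule creates, and the listed allowances use up practically all of the margin. The consequence is modest. Relative to no non-download, one-sided per-joint power falls by about 1 point at an assumed 5%, 2 points at 10% and 4 points at 20%; at 5% it still rounds to the planned 0.80.

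These figures rest on the multiplicative inflation, an even knee–hip split, independence of the losses, assumed non-download rates, and the exclusion being applied as written. They do not show a seriously underpowered trial. The unstated sidedness matters more: with no non-downloaders, the same numbers give 0.81 one-sided and 0.71 two-sided. For that reason any restated power has to name the test.

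**What to change.** First reconcile the Exclusion criteria with the intention-to-treat statement under Data analysis.

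- **If non-downloaders stay in the analysis:** delete the exclusion, both the list item and the paragraph that repeats it, and adapt the limitation in the Discussion. The target of 160 then stands on this point.
- **If the exclusion stays:** add non-download to the Sample size section as a fourth loss, in the app arm only, at a stated assumed rate. Restate the evaluable number per arm and per joint and the power at 160 recruited, and name the sidedness used. At an assumed 10%, for example, this is about 111 in total, with 26.3 app and 29.2 control patients per joint and power of 0.79 one-sided or 0.68 two-sided. At 20% it is about 105, with 23.3 and 29.2 per joint and power of 0.77 or 0.65. The dropout allowance should also say whether it includes any of these patients.

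Neither route needs additional patients. Under the second, the cost is wording and a slightly less favourable stated number and power. Under the first, the sponsor would also have to keep collecting the three-month questionnaire from patients who never used the app.

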### Data analysis

Baseline data, clinical and demographic characteristics will be presented to show the baseline comparability of the intervention group and the control group. The analysis will include all patients following the intention-to-treat principle, drop-out and loss to follow-up will be described. Data will be checked for completeness and normality. The treatment effect will be evaluated by the change in ADL using between group analyses, such as independent t-test and ANCOVA to adjust for demographic factors such as age, sex, BMI (body mass index), baseline pain, anxiety, joint, comorbidities, physical activity, pain medication, type and duration of rehabilitation and social support on change in outcomes. For comparison within groups paired t-tests will be conducted. Within the intervention group the relationship between usage metrics and patient reported outcomes will be analysed using linear regression analyses.

All statistical analyses will be performed using IBM SPSS Statistics for Windows, version 24 (IBM Corp., Armonk, N.Y., USA).

Results of the study will be presented at conferences and placed in journals.

The controlled trial will be accompanied by multi-perspective qualitative research approaches to understand user decisions and long-term user engagement of the intervention. These studies will be reported elsewhere.

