### Outcomes

Data presented in Table 1 will be measured in the study.

**Table 1 Tab1:** Study measures to be collected

Measure	Instrument	t_0_	t_1_	t_2_	t_3_	t_4_
Primary outcome measure						
Activities of daily living (ADL)	KOOS/HOOS subscale ADL (self-reported)	x				x
Secondary outcome measures						
Pain, symptoms, Sport & Rec and quality of life	KOOS/HOOS subscales pain, symptoms, Sport & Rec and quality of life (self-reported)	x				x
Pain at rest	NRS (self-reported)	x	x	x	x	x
Pain during activity	NRS (self-reported)	x	x	x	x	x
Preoperative anxiety and depression	HADS (self-reported)	x	x			
Other measures						
Usage metrics	number of user sessions, length of time participants interact with the app, content they engage with, frequency of recording self-monitoring parameters, number of awards	continuous recording				
Physical activity	IPAQ (self-reported)	x				
Social support	questionnaire (self-reported)					x
Physician visits post-surgery	questionnaire (self-reported)					x
Use of pain medication	medical record, questionnaire (self-reported)		x	x	x	x
Sex, age	medical record				x	
BMI (size, weight)	medical record				x	
Operated joint	medical record				x	
OPS, ICD	medical record				x	
Comorbidities	medical record				x	
Duration of hospital stay	medical record				x	
Type and duration of planned and performed rehabilitation programme	medical record, questionnaire (self-reported)				x	x
Complications post-surgery	medical record, questionnaire (self-reported)			x	x	x
Structural data of hospitals						
- Number of beds - Number of joint replacement surgeries performed over the past 12 months - Number of nurses in the orthopaedic departments: nurses, nursing assistants, Pain Nurses, full-time equivalent - Number of physicians in the orthopaedic departments: total number, number of orthopaedic specialists, full-time equivalent - Process quality management data for the care of patients with THR/TKR (documentation forms and guidelines, interprofessional standard operating procedures for analgesic therapy, pain management guidelines, other pain therapy guidelines, standard operating procedures for patients with THR/TKR, special contracts with other facilities and mandatory health insurance companies for structured patient care) - Regular cooperation with institutions of inpatient or outpatient rehabilitation						

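### The article promises an intention-to-treat analysis of all patients, but its exclusions after assignment and its change-score comparison do not deliver one

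*Protocol article*

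**What the plan says.** Four parts of the protocol article bear on who is analysed.

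- **Data analysis.** The population is stated as "The analysis will include all patients following the intention-to-treat principle", and of losses the section says that "drop-out and loss to follow-up will be described". The effect is to be "evaluated by the change in ADL using between group analyses, such as independent t-test and ANCOVA".
- **Outcomes, Table 1.** The ADL subscale is collected at baseline (t0) and 3 months after surgery (t4), and at no time in between. Social support, one of the named ANCOVA covariates, is collected at t4 only.
- **Exclusion criteria.** Two of the criteria can be met only after a patient has been assigned. One is a post-surgical complication. The other applies to the app arm alone: not having downloaded the app by hospital admission, repeated below the list as failing to download or access it. The Discussion lists this second exclusion as a limitation that may introduce bias.
- **Sample size.** The requirement is that "58 knee patients and 58 hip patients are required to detect a difference of 10 points". To reach it the section allows for 20% drop-out, and also for "5% complications post-surgery [50] and 4% erroneous records, a total of 160 patients will be recruited".

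**The concern.** Intention to treat means that patients are compared as assigned, whatever happens afterwards. The article claims this, and then removes patients for events that follow assignment. One of these removals acts in a single arm: app-arm patients who never engaged are taken out, while the control patients who would not have engaged stay in. The remaining comparison is closer to app users against all controls.

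Patients lost before t4 add a second gap. They have no change score, and the article says only that their loss will be described.

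The label matters because of the design. The trial is unblinded and non-randomized, and t4 is a self-report survey sent by e-mail link. Response may depend on how recovery went or on whether the patient took to the app. A reader who sees intention to treat will assume protection against such selection, and the analysis as described does not give it.

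**Working it through.** **1. Reproducing the recruitment figure.** Inputs from the Sample size section: 58 + 58 = 116 patients required; allowances of 20%, 5% and 4%. (Whether 58 per joint is itself correct is a separate matter; it is taken as given here.)

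116 / (0.80 × 0.95 × 0.96) = 116 / 0.7296 = 159.0, which agrees with the stated 160. Adding the allowances instead gives 116 / 0.71 = 163.4, a slightly worse match.

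**2. Splitting the losses out of 160.**

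| Step | Lost | Left |
|---|---|---|
| Drop-out, 20% of 160 | 32 | 128 |
| Complications, 5% of 128 | 6.4 | 121.6 |
| Erroneous records, 4% of 121.6 | 4.9 | 116.7 |

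The total set aside is 160 − 116.7 = 43.3, or 27%. Of this, 32 patients are drop-outs. The other 11.3 are patients with complications, whom the exclusion criteria remove by rule, and records judged erroneous. There is no allowance for app-arm patients excluded for not downloading or accessing the app, so the number analysed could fall below 116.7, and only the app arm would shrink.

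**3. Setting the claim against the rules.**

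| Group of patients | Data analysis section claims | What the article provides |
|---|---|---|
| App arm, app not downloaded or accessed | included | excluded; reasons recorded and reported |
| Post-surgical complication, either arm | included | excluded; 5% set aside |
| Erroneous record | included | 4% set aside |
| No t4 score | included | no change in ADL can be formed; loss described |

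For the last row, neither a t-test nor an ANCOVA on change can use a patient without t4 unless a value is supplied. There is no intermediate ADL score to supply it from, and social support is missing for that patient too.

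**4. What omission could do, by assumption only.** Let m be the share missing in an arm, and d the amount by which its missing patients score below its completers. The completers' mean exceeds the full-arm mean by m × d, so:

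bias of (app − control) = m_app × d_app − m_control × d_control

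- m = 0.20 in both arms; d_app = 5, 10 or 15; d_control = 0: bias = 1, 2 or 3 points.
- m = 0.20 and d = 10 in both arms: 2 − 2 = 0.
- m = 0.25 (app) and 0.15 (control), d = 10 in both: 2.5 − 1.5 = 1 point.
- m = 0.20 in both arms; d_app = 0; d_control = 10: 0 − 2 = −2 points, against the app.

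The documents give no value for d and no loss by arm.

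**The case against.** A reader might infer that the sample size proves a complete-case analysis, since 160 are recruited to leave about 116. It does not. Trials that analyse by intention to treat with imputation also inflate for drop-out, because missing outcomes cost information.

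A reader might also infer that naming a t-test and ANCOVA contradicts intention to treat. It does not: ANCOVA with imputed outcomes can respect it, and the article's wording leaves its list of methods open. A missing-data method may stand in a fuller protocol or analysis plan that is not shown, and its absence from a journal article is no fault.

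Nor is the 27% a missing-data rate. Drop-out is 20%, and the complications share follows an explicit exclusion rule.

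Finally, the population sentence could be read as covering all patients who remain once the exclusion criteria have been applied. That would make the text consistent, but patients removed for what happens after assignment are then outside the comparison, and the intention-to-treat label no longer fits.

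All of these narrow the point. They do not remove the conflict between a population of all patients and two exclusions that operate after assignment, one of them in a single arm. An unseen analysis plan could supply an imputation method, but it could not make those exclusions agree with the sentence in the Data analysis section.

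**Conclusion.** The conflict is real and lies in the printed text. The article claims an analysis of all patients by intention to treat. It excludes some of them after assignment, sets complications and erroneous records aside in its sample size, and describes a change analysis that, as written, only patients with a t4 score can enter. On its own allowances about 117 of 160 would remain, and fewer if app-arm patients are excluded for not downloading or accessing the app. The number is certain only as arithmetic on the stated allowances.

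The effect on the result is not known. The range of 1 to 3 points rests on an assumed deficit confined to the app arm; other assumptions give zero or the opposite sign. It shows that the choice can matter against a 10-point target, not that the estimate will be inflated. The analysis population should be reconciled before the data are analysed.

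**What to change.** Reconcile the Exclusion criteria, Sample size and Data analysis sections in one of two ways.

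**(a) Keep the claim and deliver it.** Make the primary ANCOVA an analysis of all assigned patients. Non-downloaders and patients with complications stay in the analysis set and are surveyed to t4. Impute missing t4 ADL by multiple imputation from a small model: group, joint, hospital, t0 ADL, NRS pain at t0 to t3, and the ANCOVA covariates, including social support, which is itself missing when t4 is missing. Report as sensitivity analyses the complete-case, app-user comparison and a shift analysis that lowers the imputed app-group values, for instance by 5 and 10 points.

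**(b) Drop the claim.** Remove the references to all patients and to intention to treat, and label the primary result a complete-case analysis after exclusions.

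Option (b) costs only wording. Option (a) needs no additional recruitment and no new measures, but it requires t4 surveys from patients who would otherwise be excluded, and some programming. The interval may be wider, and the estimated effect will be diluted if patients who never used the app gain nothing from it. With 116.7 / 2 ≈ 58 observed patients per arm, the imputation model must be kept small; fitting it to both arms together with group as a term is safer than fitting each arm separately. According to the Trial status section, control recruitment was still under way and the app was in final testing at submission, so the exclusion rule for the app arm could still have been changed then.

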### Study hypothesis

The primary aim of the study is to test the hypothesis that patients undergoing TKR/THR using the app RECOVER-E attain better function in activities of daily living 3 months post-surgery when compared to patients undergoing surgery without using the app (control group).

Further hypotheses assume that patients using the app RECOVER-E experience significantly less symptoms, less pain, better function in sport and recreation, as well as a better knee/hip-related quality of life 3 months post-surgery when compared to the control group. Furthermore, we hypothesize less preoperative anxiety and postoperative pain in patients using the app RECOVER-E when compared to the control group.

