**Fig. 1 Fig1:**
[figure not shown]
Flow chart of participants in the pabee study

A random assignment of the participants and simultaneous treatment of intervention and control group would carry the risk that people in the control group might learn about the app and its contents from patients of the intervention group. In order to prevent diffusion of treatment effects among participants, patients scheduled for preoperative consultation from January 2019 to May 2019 will be assigned to the control group and patients scheduled for preoperative consultation from June 2019 to October 2019 will be assigned to the intervention group.

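### The primary comparison of change in ADL does not name baseline ADL as a covariate, which costs precision and leaves the result dependent on an unstated assumption about how the two calendar cohorts differ

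*Protocol article*

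**What the plan says.** The Data analysis section of the protocol article sets the primary comparison: "The treatment effect will be evaluated by the change in ADL using between group analyses, such as independent t-test and ANCOVA". The ANCOVA is described as "ANCOVA to adjust for demographic factors such as age, sex, BMI (body mass index), baseline pain, anxiety", and the list continues with "joint, comorbidities, physical activity, pain medication, type and duration of rehabilitation and social support on change in outcomes". Counting rehabilitation once, that is eleven named factors. Baseline pain is among them; baseline ADL is not. Both the methods and the covariates are given as examples, so neither list is closed, and the section does not say whether the t-test or the ANCOVA carries the primary conclusion.

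Table 1 (Outcomes) marks the ADL subscale at t0 and at t4, so the baseline value is available. Groups are formed by calendar period: "patients scheduled for preoperative consultation from January 2019 to May 2019 will be assigned to the control group", and patients from June to October 2019 form the intervention group. The Discussion calls the lack of randomisation a major limitation and answers it with an analysis of group comparability.

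**The concern.** The baseline value of the primary outcome is usually among the strongest predictors of its follow-up value. A t-test on change fixes the baseline coefficient at one, so each point of baseline difference is taken to carry over in full to 3 months. ADL is scored from 0 to 100 and major surgery lies between the two measurements, so patients who start worse have more room to gain, and full carry-over is a strong assumption.

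Two things are at stake. The first is precision, in a trial sized for separate knee and hip analyses. The second is sensitivity to baseline differences between cohorts that were not randomised. Patients who have not downloaded the app are excluded from the intervention arm only, so a baseline difference could arise by selection as well as by chance. An analysis plan that followed the article literally could report the unadjusted change-score t-test as the main result.

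**Working it through.** **Inputs from the protocol article.** Difference 10 points, SD 15, power 0.80, α 0.05 (sidedness not stated), 58 patients per joint, 1:1 assignment and so 29 per arm, 160 in total (Sample size; Design).

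**Assumptions, not in the article.** Pre-post correlation r of 0.3, 0.5 or 0.7; equal SDs at t0 and t4; a 5-point baseline imbalance as illustration; a correlation of baseline pain with baseline ADL of 0.6 to 0.8. The article does not say whether SD 15 belongs to the score or to the change.

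**1. The plan's own figure.** n per arm = 2(z_α + z_β)² × SD²/δ².
- One-sided: 2 × (1.645 + 0.842)² × 225/100 = 27.8, so 28. The exact t-test gives 28.5, so 29 per arm and 58 per joint, as stated.
- Two-sided: 36 per arm (exact t-test 37, or 74 per joint), which does not match 58.
- Total: 116/(0.80 × 0.95 × 0.96) = 159.0, close to 160.

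**2. Precision.** Var(change) = 2s²(1 − r) and Var(baseline-adjusted) = s²(1 − r²). The ratio of adjusted to change is (1 + r)/2. The table takes SD 15 as the SD of change, with 29 per arm and the normal approximation.

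| r | (1 + r)/2 | Variance of change relative to adjusted | SD after adjustment | Two-sided power | One-sided power |
|---|---|---|---|---|---|
| no adjustment | – | – | 15.00 | 0.72 | 0.81 |
| 0.3 | 0.65 | 1.54 | 12.09 | 0.88 | 0.93 |
| 0.5 | 0.75 | 1.33 | 12.99 | 0.83 | 0.90 |
| 0.7 | 0.85 | 1.18 | 13.83 | 0.79 | 0.87 |

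The exact t-test puts the unadjusted two-sided power at 0.70. If SD 15 is instead the SD of a single score, two-sided power goes from 0.57 to 0.76 (r = 0.3), from 0.72 to 0.83 (r = 0.5) and from 0.91 to 0.95 (r = 0.7).

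**3. Baseline imbalance d (intervention minus control).**
- If t4 ADL depends linearly on observed t0 ADL with slope r, the change-score difference is off by −(1 − r)d. For d = 5 that is −3.5, −2.5 or −1.5 points. The baseline-adjusted estimate is off by 0.
- If the cohorts differ by a stable amount and would move in parallel, the change score is off by 0 and baseline-adjusted ANCOVA by +(1 − r)d, that is +3.5, +2.5 or +1.5.

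A simulation with 400,000 patients reproduced both results to within 0.1 point.

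**4. What baseline pain already recovers.** In the first scenario, an ANCOVA of change with baseline pain but not baseline ADL reduced the error as follows:
- r = 0.3: from −3.5 to between −2.3 and −1.2
- r = 0.5: from −2.5 to between −1.6 and −0.95
- r = 0.7: from −1.5 to between −0.95 and −0.56

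**5. Plausibility of 5 points by chance.** With an assumed baseline SD of 15, the SE of a baseline difference is 15 × √(2/29) = 3.9 points per joint, so 5 points or more in either direction has probability about 0.20. With both joints pooled (58 per arm) the SE is 2.8 and the probability about 0.07.

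**The case against.** A reader might infer that the plan rules out baseline ADL. It does not: both lists are given as examples, and in a condensed article the final model may be left to an analysis plan that is not shown. That stands, and it makes this an omission from a long list, not an exclusion. It does not remove the point, because the article commits to change as the outcome form and to a t-test that can adjust for nothing.

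A reader might also infer that any imbalance between the cohorts becomes bias. The documents do not support this. Allocation is by calendar period, and nothing in the article says why the cohorts would differ. Under stable differences with parallel trends the change score is the unbiased estimator and ANCOVA the biased one (Lord's paradox). Nor should chance imbalance be charged as a separate bias: averaged over samples it is already contained in the variance ratio of step 2.

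The size depends on choices too. The bare t-test is the least favourable comparator, and the planned ANCOVA loses less. The per-joint case is also the harder one; listing joint as a covariate points to a pooled model as well. The two-sided starting power of 0.70-0.72 comes from the unstated sidedness of α, a separate matter, and not from the use of a change score.

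Finally, the Study hypothesis speaks of patients who "attain better function in activities of daily living 3 months post-surgery", while the analysis uses change. This is not a contradiction: the Sample size section frames the same aim as greater improvement.

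**Conclusion.** The point holds as one of precision and specification. The article omits the baseline value of its primary outcome from an otherwise long covariate list and does not choose between an unadjusted and an adjusted test. The unadjusted change score has 1.54, 1.33 or 1.18 times the variance of the baseline-adjusted estimate at r = 0.3, 0.5 or 0.7, given equal SDs; r is assumed throughout. The loss is smaller against the planned ANCOVA.

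The bias element is conditional. A 5-point imbalance moves the change-score estimate by 1.5 to 3.5 points against a 10-point target if outcome depends on observed baseline, and by nothing under parallel trends. Baseline adjustment therefore does not by itself cure confounding between the calendar cohorts. Severity: should-fix.

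**What to change.** Name one primary model: ANCOVA of t4 ADL on arm, with t0 ADL as a mandatory covariate, plus joint and the other covariates measured at baseline. With t0 ADL in the model, the arm effect is the same whether t4 ADL or the change is the dependent variable, so the aim of comparing improvement is kept. Retain the change-score comparison as a stated sensitivity analysis, and say that it rests on parallel trends while the primary model rests on conditioning on observed baseline. If the two disagree, that should be reported as uncertainty about confounding.

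The cost is wording. ADL is already collected at t0, and no added patients or visits are needed. According to Trial status, control recruitment was still under way at submission in May 2019, so the model could be fixed before any comparison of outcomes. The small downside is reliance on the baseline-conditional assumption, which the sensitivity analysis checks.
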